**7.2 Dose modifications table 1.**

| Adverse effect | Grade | Dose reduction | | |
| --- | --- | --- | --- | --- |
| First time | Second time | Third time |
| Neutropenia or leukopenia | Ⅳ | Irinotecan reduce to 75%-80% | Irinotecan reduce to 50% | withdraw |
| Febrile neutropenia | Ⅲ |
| Thrombocytopenia and bleeding | Ⅳ | withdraw |  |  |
| Thrombocytopenia without bleeding | Ⅲ-Ⅳ | Irinotecan reduce to 75%-80% | Irinotecan reduce to 50% | withdraw |
| Non-hematologic toxicity (diarrhea, intestinal obstruction etc.) | Ⅳ | withdraw |  |  |
| Ⅲ | Irinotecan reduce to 75%-80% | Irinotecan reduce to 50% | withdraw |
| AST, ALT and serum creatinine meet the exclusion criteria and cannot be corrected in a week |  | withdraw |  |  |
| Bilirubin >1.5 - ≤ 3 times of upper limit of normal（ULN） |  | Irinotecan reduce to 50%-60% | withdraw |  |
| Bilirubin > 3 times of ULN |  | withdraw |  |  |

**Note：**

1. For patients who had prior pelvic radiotherapy within one year before chemotherapy, CPT-11 was reduced to 75% to 80%
2. Hematologic toxicity needs to recovered to ≤ Grade 1 before chemotherapy
3. Clinical standard operating procedure (SOP) of chemotherapy delay due to toxicities

Normal schedule d1→d8→d15→d22→d29→d36→d43→d50→d57

Delayed < 1week d1→d8→d15→d18→d29→d32→d36

Delayed > 1week d1→d8→d15→d22→d25→d29→d36→

副反应恢复

1. **Tests before chemotherapy**

Blood count

Blood biochemical (15 liver function, kidney function 4, two of lipids, electrolytes four fasting glucose, LDH)

Routine urine

Time for tests: chemotherapy ± 3 days

CT/MRI for baseline evaluation

1. **Tumor response evaluation**

According to RECIST1.1, evaluate every 6 weeks’ chemotherapy.

1. **Adverse effects evaluation**

National Cancer Institute Common Toxicity Criteria 4.0

1. **Staging**

AJCC 7th edition (2010) TNM staging system for colon/rectal cancer

1. **Sample size calculation and Statistical method**

12.1 Sample size calculation

**Candidate gene study**

we choose type I error α = 0.05, 1-β = 0.8, two-sided test, provided the target SNP allele frequency in the population was about 20%, treatment efficacy was about 30%, OR ≥ 3.5, the calculated samples size was ≤ 86.

**GWAS study**

We set statistical limits for the type I error α = 0.01, 1-β = 0.8, two-sided test, provided the target SNP frequency in the population > 15%, and OR> 4, according to the known lowest FOLFIRI first-line treatment induced severe adverse reactions (about 20%) and treatment efficacy (about 30%), we calculate that the needed samples will be 112 by software Quanto (Version 1.2.4), 1:1 ratio.

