What’s more, in different populations, genotype variants are more or less frequent. Remarkable interethnic differences in the distributions of UGT1A1 genetic polymorphisms have been known. The allele frequency of UGT1A1*28 among Caucasians is higher (0.3 to 0.4) than that among Asians (0.1 to 0.2). On the contrary, other variant alleles in the coding regions were found only in Asians.[13](#_ENREF_13)

Does Topo1 immunohistochemistry have any effect on the clinical response or prognosis for colorectal cancer patients treated with 5-FU/CPT-11 regimen? It is debated now. Some studies showed that it does not differ in TS or Topo-1 expression level in tumor.[14](#_ENREF_14) But some indicated that patients with moderate/high level of Topo-1 benefited from CPT-11.[15](#_ENREF_15) How about Topo1 gene polymorphism? Hoskins demenstrated that TOP1 and TDP1 htSNPs were related to grade 3/4 neutropenia (P = 0.04) and response (P = 0.04), respectively. [16](#_ENREF_16)But that’s not enough.

For the three limitations mentioned in the preface part, we think it is essential to carry out a prospective study in the relationship between the irinogenetics and CPT-11 toxicity, as well as the effectiveness or clinical outcome in China.

1. **Candidate genes**

- Topo1
- Carboxylesterase (CES)
- CYP3A4 cytochrome P450, family 3, subfamily A, polypeptide 4
- UGT1A1
- [ATP-binding cassette (ABC) transporters](http://en.wikipedia.org/wiki/ATP-binding_cassette_transporter)

1. **Objective and endpoints**

**Objective:** To determine the correlation between irinogenetics and irinotecan -related severe toxicities or tumor response in Chinese mCRC patients.

**Primary endpoints:** The correlation between SNP and ORR. The correlation between SNP and adverse events of Grade ≥3 (blood toxicities, diarrhea and any other serious adverse event).

**Secondary endpoints:** The correlation between SNP and PFS/OS.

1. **Research design**

Patients who meet the inclusion criteria 1-12

Record the clinical message

Collect blood samples after the consent of patients

Evaluation of target lesions

AE/toxicity

eg: diarrhe

neutropenia ect.

OS

PFS

Blood samples of each patient

Genoe-wide association study or relavant candidate gene study

The associations of each polymorphism with tumor response, toxicity, and clinical outcome (survival) will be analyzed.

1. **Method**

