**Genome-wide association study**

The GWAS will be conducted using an Affymetrix Genome-Wide Human SNP Array 6.0, followed by a systematic quality control step before the association analysis.

1. **Inclusion and Exclusion criteria**

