12.2 Statistical method

Hardy-Weinberg equilibrium will be assessed. The χ2 test will be used to compare the observed genotype frequencies with those expected under Hardy-Weinberg equilibrium.

The associations of each polymorphism with tumor response, toxicity, and demographic variables were examined using contingency tables and the Fisher’s exact test. Multivariate Logistic Regression will be performed to ascertain which genotype independently predicted response or toxicity. Odds ratios (OR) and their 95% confidence interval (CI) were calculated as estimates of the correlations. Kaplan–Meier estimates the PFS and OS. To evaluate the relationship between genotypes and PFS, IR-TTF, and OS, multivariate Cox regression (forward LR) performed, adjusting for potential confounding covariates. Hazard ratios (HR) and their 95% CI were calculated as estimates of the correlations. A value of *p* < 0.05 was considered statistically significant in a two-tailed test.

Statistical analyses were performed using SPSS16.0 (SPSS Inc, Chicago, IL) and two-sided P-value of 0.05 is considered significant.

1. **Research institutions**

Sponsor

- Tongji Hospital, Tongji Medical College, Science and Technology of Huazhong University

Collaborators

- Union Hospital, Tongji Medical College, Science and Technology of Huazhong University
- Zhongnan Hospital, Wuhan University
- Wuhan 8th Hospital, Wuhan, People’s Republic of China
- Wuhan Pu-Ai Hospital, Tongji Medical College, Huazhong University of Science and Technology
- Hubei Cancer Hospital

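### If the genome-wide option is run, the protocol has no valid significance rule for it: it is sized at a single-test α of 0.01, and the only decision rule is p < 0.05 per polymorphism.

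*Protocol*

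**What the plan says.** The Research design section leaves the genotyping strategy open: "Genoe-wide association study or relavant candidate gene study". The Method section says of the first option: "The GWAS will be conducted using an Affymetrix Genome-Wide Human SNP Array 6.0". It mentions a quality control step before the association analysis, but no genome-wide threshold, multiplicity correction or replication step. No section gives the number of SNPs to be tested.

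Section 12.1 (GWAS study) sets the planning level: "We set statistical limits for the type I error α = 0.01, 1-β = 0.8, two-sided test". The other inputs are "provided the target SNP frequency in the population > 15%, and OR> 4", a severe toxicity rate of about 20% and an efficacy rate of about 30%. The result is "the needed samples will be 112 by software Quanto (Version 1.2.4), 1:1 ratio".

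Section 12.2 defines the unit of testing: "The associations of each polymorphism with tumor response, toxicity, and demographic variables were examined using contingency tables and the Fisher’s exact test". It states the 0.05 level twice, the second time as "two-sided P-value of 0.05 is considered significant". It does not name the GWAS, either to include it or to exempt it. The Objective and endpoints section lists two primary endpoints: the correlation of SNPs with response rate, and with adverse events of grade 3 or higher.

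**The concern.** An α of 0.01 or 0.05 limits the error of one test. A genome-wide array involves a very large number of tests, repeated for each endpoint. At a per-SNP level of this size, the expected number of chance findings is the SNP count times α, and it runs into thousands. Any true marker would sit unmarked among them. The Background section criticises earlier work for small samples and conflicting results and aims at markers that can be relied on, so the primary claim of the study is affected.

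This is not a detail left to a statistical analysis plan. The protocol itself sets a planning level and a decision level, and neither suits a genome-wide scan. An analysis plan that applied a genome-wide threshold would depart from section 12.2 as written.

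**Working it through.** **1. Reproduce 112.** Inputs from section 12.1: allele frequency q = 0.15, odds ratio 4, event rate 20%, two-sided α = 0.01, power 0.80, 1:1. Assumed, because not stated: Hardy-Weinberg genotypes, a dominant model and the expected likelihood-ratio method for an unmatched case-control design.

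- Carriers: 1 − 0.85² = 0.2775.
- Event risk in non-carriers p₀ solves 0.7225·p₀ + 0.2775·4p₀/(1 + 3p₀) = 0.20. This gives p₀ = 0.132, and 0.378 in carriers.
- Carrier fraction: cases 0.2775 × 0.378/0.20 = 0.524; controls 0.2775 × 0.622/0.80 = 0.216.
- Expected likelihood-ratio statistic per subject at 1:1: λ = 0.1043.
- N = (z₀.₉₉₅ + z₀.₈₀)²/λ = (2.576 + 0.842)²/0.1043 = 112.0, that is 56 cases and 56 controls.

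So 112 is correct for one SNP tested at 0.01 in a balanced sample.

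**2. Chance findings per endpoint.** Expected number = M × α if no SNP is associated. M is assumed.

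| SNPs tested (M) | p < 0.01 | p < 0.05 |
|---|---|---|
| 100,000 | 1,000 | 5,000 |
| 500,000 | 5,000 | 25,000 |
| 1,000,000 | 10,000 | 50,000 |

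Fisher's exact test is conservative. At N = 112 with 22 or 34 events (20% or 30%), its true size at nominal 0.05 is about 0.03–0.04 for minor allele frequency 0.10 or more, and about 0.01–0.03 at 0.05 or less. A size of 0.03–0.04 still gives 3,000–4,000 findings at M = 100,000 and 30,000–40,000 at M = 1,000,000. At nominal 0.01 the simulated size is about 0.006–0.0075, which gives 600–750 and 6,000–7,500. Linkage disequilibrium clusters the false positives but leaves their expected number unchanged.

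**3. Power of 112 patients.** Power = Φ(√(112·λ) − z₁₋α/₂), with z = 2.576 at 0.01 and 5.451 at 5×10⁻⁸. Example (dominant, 20%, 1:1): √(112 × 0.1043) = 3.417; 3.417 − 5.451 = −2.034; Φ = 2.1%. For an unselected cohort with the same inputs, λ = 0.0698 and √(112 × 0.0698) = 2.795; 2.795 − 5.451 = −2.656; Φ = 0.4%.

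| Model, event rate | 1:1, α = 0.01 | Cohort, α = 0.01 | 1:1, 5×10⁻⁸ | Cohort, 5×10⁻⁸ |
|---|---|---|---|---|
| Dominant, 20% | 80% | 59% | 2.1% | 0.4% |
| Dominant, 30% | 78% | 70% | 1.7% | 0.95% |
| Additive, 20% | 90% | 73% | 5.3% | 1.2% |
| Additive, 30% | 86% | 81% | 3.7% | 2.3% |

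The cohort columns matter because 112 consecutive patients with a 20% event rate yield about 0.20 × 112 = 22 cases, not 56.

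**4. Splitting over two primary endpoints.** 0.05/(2 × 1,000,000) = 2.5×10⁻⁸ (z = 5.573). The same formula gives 0.3–1.7% power as a cohort and 1.2–4.1% at 1:1. With M = 100,000 the level is 2.5×10⁻⁷ (z = 5.158), and power stays below 10% in every row.

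**5. Size needed.** For 80% power at 5×10⁻⁸ (dominant, 20%), N is about 380 at 1:1 and 568 as a cohort.

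**The case against.** **The plan is conditional.** The design allows the genome-wide study or the candidate gene study. A reader might infer that thousands of SNPs will certainly be declared significant; the documents do not support that. The point holds only if the genome-wide option is run. The Method section and 12.1 do prepare for it.

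**Section 12.2 may be meant for candidate genes only.** It does not mention the GWAS, its methods suit a short SNP list, and its 0.05 equals the planning level of the candidate gene study. On that reading 0.01 is the GWAS's own limit. A flat contradiction between 0.01 and 0.05 is therefore a tempting inference that the text does not force. The wording about each polymorphism can equally cover the array, and no other decision rule exists. Under either reading the level is uncorrected: the count changes from the 0.05 column to the 0.01 column, and the conclusion does not.

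**The mismatch does no harm in itself.** This is true. Sizing at 0.01 and testing at 0.05 raises power per SNP. The fault is multiplicity.

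**The counts rest on an assumed SNP number.** This is also true, so a tenfold range is shown. A reader might go further and conclude that essentially every significant SNP would be false. That needs a number of true associations, which the documents do not give.

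**Severity.** No treatment decision in the protocol depends on genotype, and the threshold can be corrected before analysis. This limits the harm to the claims made from the study; it does not make the rule valid.

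**Conclusion.** The concern holds, conditional on the genome-wide option being carried out. The stated levels are wrong for a genome-wide scan. Expected chance findings per endpoint are about 1,000–10,000 at nominal 0.01 and 5,000–50,000 at nominal 0.05, somewhat fewer with Fisher's test. These counts assume 100,000–1,000,000 SNPs and no true association.

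At 5×10⁻⁸ the sample of 112 has almost no power for the planned effect: 0.4–2.3% as an unselected cohort and 1.7–5.3% at 1:1. The ranges cover dominant and additive models and event rates of 20% and 30%, at the lower bounds given in 12.1 for allele frequency and odds ratio. A reader might infer that 112 was miscalculated. It was not: it reproduces exactly, but only for one SNP at 0.01 with equal numbers of cases and controls.

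**What to change.** - **Section 12.2:** exempt the GWAS from the 0.05 rule. Claim GWAS significance only at 0.05/(number of SNPs passing quality control × 2 primary endpoints). A fixed 2.5×10⁻⁸ per endpoint is an acceptable alternative: it is the same level when one million SNPs are tested and stricter when fewer are. Name one of the two before analysis. If the components of the toxicity endpoint are tested separately, the divisor must count them. Report other top-ranked SNPs as hypothesis-generating candidates for replication.
- **Section 12.1:** state that 112 gives 80% power only for one pre-specified SNP at α = 0.01 with 56 cases and 56 controls (dominant model, 20% event rate). Add that an unselected cohort of 112 has about 59% (dominant) to 73% (additive) for 20% toxicity and about 70–81% for 30% response, and that power at 5×10⁻⁸ is only a few percent. Keeping the 80% without these conditions would overstate power in a consecutive cohort.
- **Background, and Objective and endpoints:** align the aim and the primary endpoints with a hypothesis-generating GWAS.

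The cost is wording in several sections, with no added patients, visits or assays. The downside is that the GWAS will probably yield no confirmed hit, which is the realistic expectation at this size.

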**Relavant candidate gene study**

Gene Oncology ([http://www.geneontology.org](http://www.geneontology.org/)) and the National Center for Biotechnology Information (NCBI) Gene database (<http://www.ncbi.nlm.nih.gov/gene>) and related literature to identify all functional single nucleotide polymorphisms (SNPs) of relavant genes with a minor allele frequency of more than 0.15 and a location in the promoter untranslated region or coding region of the gene.

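### The GWAS size of 112 is stated for every SNP frequency above 15%, but the dominant 1:1 model that best reproduces it gives 80% power only up to a frequency of about 0.32 to 0.34

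*Protocol*

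**What the plan says.** The GWAS paragraph of section 12.1 sets the error limits ("We set statistical limits for the type I error α = 0.01, 1-β = 0.8, two-sided test") and then the genetic condition: "provided the target SNP frequency in the population > 15%, and OR> 4". It names two outcome rates, "severe adverse reactions (about 20"%) and "treatment efficacy (about 30"%), and arrives at 112 samples from Quanto with a 1:1 ratio. It gives no inheritance model and no upper frequency.

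The candidate-gene paragraph of section 12.1 uses alpha 0.05, 80% power, an OR of at least 3.5 and a 30% efficacy rate, "provided the target SNP allele frequency in the population was about 20"%, and arrives at no more than 86. The Method section selects candidate SNPs "with a minor allele frequency of more than 0.15", which in principle means 0.15 to 0.50.

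**The concern.** Writing the frequency as a lower bound, next to a lower bound on the OR, presents 15% as the least favourable case: 112 would then give 80% power or better for any more common SNP. That depends on the genetic model. If carriers are compared with non-carriers (dominant), information is lost when either group becomes scarce, and non-carriers fall to 25% of the population at allele frequency 0.50. Power then has an upper limit in frequency as well as a lower one, and a single open-ended condition cannot be right.

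What is at stake is the stated chance of detecting a true OR of 4 for common SNPs. With a dominant effect at frequency 0.50, it would be missed 41% to 45% of the time instead of 20%.

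**Working it through.** **Inputs.** From section 12.1, GWAS study: two-sided alpha 0.01, power 0.80, OR 4 (the boundary value), frequency 0.15, event rates 20% and 30%, 1:1. I read the frequency as an allele frequency, as the candidate paragraph does, 1:1 as cases to controls, and 112 as their total. Hardy-Weinberg proportions are assumed.

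**Method.** Let q be the allele frequency and C = 1 − (1 − q)² the carrier frequency. Solve for event risks p0 (non-carriers) and p1 (carriers) with odds ratio 4 and C·p1 + (1 − C)·p0 = event rate. Let a and b be the carrier proportions in cases and controls, and m = (a + b)/2. The expected likelihood-ratio statistic per case-control pair is

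Λ = 2[a ln(a/m) + (1−a) ln((1−a)/(1−m)) + b ln(b/m) + (1−b) ln((1−b)/(1−m))].

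Pairs for 80% power = (2.576 + 0.842)²/Λ = 11.68/Λ. Power with 56 pairs = Φ(√(56Λ) − 2.576).

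**Reproducing 112.** At q = 0.15 and a 20% rate:
- C = 0.2775, p0 = 0.132, p1 = 0.378.
- a = 0.2775 × 0.378/0.20 = 0.524; b = 0.2775 × 0.622/0.80 = 0.216.
- Λ = 0.2085, so 11.68/0.2085 = 56.0 pairs, or 112 in total.

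At the 30% rate the same model gives 118. An additive model gives 89 (20%) or 97 (30%), and a recessive model 887 or 1,044.

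**Cross-check on the candidate study.** q = 0.20, OR 3.5, 30% rate, alpha 0.05: a = 0.566, b = 0.272, Λ = 0.1813. Then 7.849/0.1813 = 43.3 pairs, or 86.6 in total against the printed 86. An additive model gives 65. Two sizes with different inputs therefore point to the dominant model.

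**Power at N = 112 as frequency rises.** For example, at q = 0.50 and a 20% rate: C = 0.75, a = 0.908, b = 0.711, Λ = 0.1308, √(56 × 0.1308) = 2.706, and Φ(0.130) = 55%. The cohort columns use the same test with 20% or 30% of the 112 as cases.

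| Frequency | 1:1, 20% rate | 1:1, 30% rate | Cohort, 20% rate | Cohort, 30% rate |
|---|---|---|---|---|
| 0.15 | 80.0% | 77.5% | 59% | 70% |
| 0.25 | 83.5% | 83.8% | 60% | 76% |
| 0.32 | 80.0% | 81.6% | 55% | 72% |
| 0.34 | 78.3% | 80.2% | 53% | 70% |
| 0.40 | 71.6% | 74.4% | 45% | 63% |
| 0.50 | 55.2% | 59.0% | 31% | 47% |

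With 56 cases and 56 controls, 80% is held from 0.150 to 0.320 (20% rate) and from 0.168 to 0.343 (30% rate). At frequency 0.50, 80% power would need 89.3 pairs (about 180 in total) or 83.2 pairs (about 168).

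**Expected split.** 112 × 0.20 = 22.4 events and 112 × 0.30 = 33.6 events, not 56. Dominant power then peaks at 61% and 76%, so it does not reach 80% at any frequency.

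**Additive effect and additive test, 1:1.** Power from 0.15 to 0.50 is 90% to 98% (20% rate) and 86% to 98% (30% rate).

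**Candidate study at N = 86, dominant, 1:1.** 75% at 0.15, 80% at 0.20, 74% at 0.40, 62% at 0.50.

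**The case against.** The strongest objection is that the protocol never says the model is dominant. The fall in power exists only under that assumption. With an additive effect and test, 15% is a correct floor. This stands: a reader might infer a proven arithmetic error, and the documents do not support that. They show an open-ended condition that conflicts with the model best fitting the printed numbers.

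Nor is the dominant model the only conceivable source of 112. A single cohort with an additive effect and a 30% rate needs about 110. But that contradicts the stated 1:1 ratio, and at the 20% rate it needs about 128. The dominant model, for its part, matches 112 only at the 20% rate.

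The OR is also written as an inequality. At frequency 0.40, 112 reaches 80% once the OR is about 4.4 to 4.6, a small shortfall. At 0.50 it takes about 6.0 to 6.7, so the large shortfall is confined to the most common SNPs.

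A reader might also infer that the candidate paragraph overclaims in the same way. It does not: it ties its size to a frequency of about 20%, and the Method section's threshold is a selection rule, not a power statement. Likewise, nothing in the protocol says that a non-significant SNP will be read as showing no association, so that consequence is a risk and not a stated plan.

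Finally, it would be tempting to replace the condition with 0.15 to 0.32 and stop there. That range fails at 0.15 for the 30% rate (77.5%), which belongs to response, a primary endpoint. It also takes a 1:1 split as given, although the Research design describes patients enrolled prospectively with no selection of cases and controls.

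**Conclusion.** The concern holds in a limited form. If 112 was obtained from a dominant model, as both printed sizes suggest, the claim of 80% power for all frequencies above 15% is too broad. In the 1:1 design the supported range is about 0.15 to 0.32 at the 20% rate and about 0.17 to 0.34 at the 30% rate, and power at 0.50 is 55% to 59%. This rests on an inferred model, Hardy-Weinberg proportions, an OR of exactly 4, and 56 cases with 56 controls. The last assumption matters most, because the expected event split gives dominant power below 80% everywhere. What is certain without any inference is that section 12.1 omits the model on which its frequency condition depends.

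**What to change.** In section 12.1, GWAS study:

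- Name the genetic model used in Quanto.
- If it is dominant, replace the open-ended frequency condition with the supported range for each endpoint (about 0.15 to 0.32 for severe adverse reactions, about 0.17 to 0.34 for response). State the power at 0.40 (72% and 74%) and at 0.50 (55% and 59%).
- Label these figures as conditional on 56 cases and 56 controls, or recompute them for about 22 and 34 events in 112 patients and make no 80% claim for a dominant effect.
- If the model is additive, say so and show how 112 follows, since the 1:1 additive calculation gives 89 to 97.

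In the candidate-gene paragraph, add only that 86 supports 80% power near frequency 0.20 under the same 1:1 dominant assumption, and not over the whole range that the Method section selects.

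The cost is a few sentences and one rerun of the calculation. No extra patients are needed; the stated power becomes less favourable.

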Pharmacogenomics Study of CPT-11 as the First-line Chemotherapy for Metastatic Colorectal Cancer

1. **Background**

Colorectal cancer (CRC) is the third leading cause of cancer-related deaths in China and leads to nearly 180,000 deaths per year. Irinotecan (CPT-11) combined with 5-FU/LV (FOLFIRI) is recommended as one of the first-line chemotherapy regimens for Metastatic Colorectal Cancer (mCRC).The variation seen in patient response and tolerability remains a clinical challenge. Some clinical studies showed a significant relationship between the gene polymorphisms in key enzymes (eg.UGT1A1, ABCB1, SLCO1B1 etc) involved in the metabolism of CPT-11 and its toxicity. But there are three limitations. Firstly, most of the studies were either retrospective analysis or with small sample size and some of the results were conflict. Secondly, Chinese were rarely included. Thirdly, most of them only used candidate gene approach. By using prospective method, in our study, a larger sample will be enrolled and our aim is to find reliable genetic markers for predicting clinical outcome and toxicity in mCRC patients treated with CPT-11 chemotherapy.

When diagnosed with colorectal cancer, 35% of those patients are stage Ⅳ. Approximately 50%-60% of patients diagnosed with colorectal cancer will develop metastases. Irinotecan is a camptothecin analogue with strong antitumor activity through inhibition of topoisomerase I. Objective response rate (ORR) is about 35%-50%.Compared with treatment with 5-FU/LV, treatment with irinotecan, fluorouracil, and leucovorin resulted in significantly longer progression free survival, higher rate of confirmed response, and longer overall survival. Toxicities associated with irinotecan include both early and late forms of diarrhea (Grade3 to 4 are 22%-30%), and neutropenia (Grade3 or 4 are about 50%). The V308 study had demonstrated that FOLFIRI followed by FOLFOX6 led to longer median Progression-free survival (PFS) and better tolerability in second-line therapy than the reverse sequence.[6](#_ENREF_6) Due to being afraid of the toxicity (e.g. fatal diarrhea) of CPT-11，most doctors in China would like to choose FOLFOX instead of FOLFIRI.

Patients respond differently to identical medications. How to match the right drug to the right person? Nowadays, personalized therapy based on the genotype represents the future direction in cancer treatment.

**
[figure not shown]
**

Fig. 1: **The metabolism of CPT-11** .[7](#_ENREF_7)

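### The GWAS sample size of 112 delivers its stated 80% power only at a 20% event rate with 1:1 sampling; in the planned cohort it gives about 70% for response and 71% for neutropenia

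*Protocol*

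**What the plan says.** Section 12.1, GWAS study, sets the error rates as "We set statistical limits for the type I error α = 0.01, 1-β = 0.8, two-sided test". The genetic inputs are "provided the target SNP frequency in the population > 15%, and OR> 4". The event rates come in one clause, "according to the known lowest FOLFIRI first-line treatment induced severe adverse reactions (about 20%) and treatment efficacy (about 30"%), and the result follows: "we calculate that the needed samples will be 112 by software Quanto (Version 1.2.4), 1:1 ratio". The paragraph does not say which of the two rates produced 112, and it names no genetic model (dominant, log-additive or recessive).

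The Objective and endpoints section makes two associations primary: SNP with ORR, and SNP with Grade ≥3 adverse events, where blood toxicities are the first kind listed. The Background reports "neutropenia (Grade3 or 4 are about 50"%), Grade 3-4 diarrhoea of 22%-30%, and "Objective response rate (ORR) is about 35%-50"%.

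The Background calls the study prospective. The Research design scheme enrols patients who meet the entry criteria, takes blood, and follows them for response, toxicity and survival. Nothing describes selecting patients by outcome.

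**The concern.** A required sample size depends on the event rate, so a single figure cannot give exactly 80% power at both 20% and 30%. If 112 belongs to one rate, the 80% is not established for the other primary endpoint. Neither rate covers Grade 3-4 neutropenia, which the protocol itself puts at about 50% and which falls under a named part of the toxicity endpoint.

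The 1:1 ratio matters as well. In a case-control calculation 112 means 56 cases and 56 controls. A cohort of 112 yields about 112 × 0.20 = 22 cases at a 20% rate, or 112 × 0.30 = 34 at 30%.

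At stake is how a null result is read. A reader told that the design had 80% power for both primary endpoints would place more weight on a negative finding than the design supports.

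**Working it through.** **Inputs.** Section 12.1, GWAS study: alpha 0.01 two-sided, power 0.80, odds ratio 4 and SNP frequency 0.15 (both at their stated lower bounds), rates 20% and 30%, ratio 1:1. Background: neutropenia 50%. Inferred: 15% is an allele frequency, and the effect is dominant.

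**Formulas.**
- Carrier frequency under Hardy-Weinberg: 1 − 0.85² = 0.2775.
- For event rate K, the risks p0 (non-carriers) and p1 (carriers) satisfy odds(p1) = 4 × odds(p0) and 0.7225·p0 + 0.2775·p1 = K.
- Carrier share among cases = 0.2775·p1/K; among controls = 0.2775·(1 − p1)/(1 − K).
- Likelihood-ratio gain per subject: G = H(f) − Σ m_g·H(f_g). Here H(p) = −p ln p − (1−p) ln(1−p), f is the case fraction in the sample, m_g the share of genotype g in the sample, and f_g the case fraction within genotype g.
- N = (2.576 + 0.842)²/(2G) = 11.679/(2G). Power at 112 = Φ(√(2·112·G) − 2.576).

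**Reproducing 112 (K = 0.20, 1:1).** p0 = 0.132 and p1 = 0.378. Carriers are 0.524 of cases and 0.216 of controls, so m = 0.370 for carriers and 0.630 for non-carriers. The case fractions within genotype are 0.708 and 0.378. G = 0.6931 − (0.370 × 0.6037 + 0.630 × 0.6629) = 0.0521, and N = 112.0. A two-proportion formula on the carrier shares also gives 2 × 56 = 112.

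**Checking the inferred model on the candidate-gene figure.** Alpha 0.05, allele frequency 0.20 (carriers 0.36), odds ratio 3.5, response 30%, 1:1. Carriers are 0.566 of cases and 0.272 of controls, G = 0.0453, and N = 7.849/(2 × 0.0453) = 86.6. The two-proportion formula gives 86. The protocol states at most 86.

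**Other 1:1 settings at 20%/30%/50%.** Log-additive gives 89/97/116. Dominant with 15% as carrier frequency gives 162/180/220. Dominant with the rate as baseline risk gives 117/124/141. Recessive gives at least 887. None returns 112.

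**Dominant model, 1:1 as stated:**

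| Event rate | G | N for 80% | Power at 112 |
|---|---|---|---|
| 20% | 0.0521 | 112.0 | 80.0% |
| 30% | 0.0496 | 117.8 (118) | 77.5% |
| 50% | 0.0438 | 133.3 (134 in whole pairs) | 71.1% |

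**Cohort, with f equal to the event rate:**

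| Event rate | G, dominant | N, dominant | Power at 112, dominant | N, log-additive | Power at 112, log-additive |
|---|---|---|---|---|---|
| 20% | 0.0349 | 167 | 58.7% | 128 | 73.2% |
| 30% | 0.0431 | 136 | 70.2% | 110 | 80.8% |
| 50% | 0.0438 | 133 | 71.1% | 115.5 | 78.5% |

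At 50% the cohort is itself 1:1, so that row is the same in both dominant tables.

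**The case against.** **The genetic model is inferred.** This stands as a caveat. Under a log-additive model a cohort of 112 does reach 80% at 30% response. A log-additive cohort calculation at 30% even comes near 112, at 110. That setting ignores the stated 1:1 ratio, however, and it gives 74 rather than 86 for the candidate-gene study. The dominant 1:1 reading fits both figures.

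**The shortfall at 30% is small under 1:1.** It is 6 patients, or 2.5 points, against rates given only approximately and inputs given as lower bounds. An allele frequency of 0.17 or an odds ratio of 4.15 would close it. This too is fair. But the 80% is claimed at the bounds, and the larger loss at 30% comes from the cohort's case fraction, not from the event rate.

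**Toxicities may be analysed by type.** The endpoint does not say that they are pooled. Diarrhoea at 22% would need 113 under 1:1, close to 112, but 158 in a cohort. Neutropenia alone stays at about 50%. A reader might go further and infer a composite rate well above 50% by combining neutropenia with diarrhoea. The protocol gives no information on their overlap and defines no pooled endpoint, so that step is unsupported.

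**The lowest rate may be a deliberate safeguard.** A reader of the 1:1 table might infer that the lowest rate is the favourable choice, because N rises with the rate there. That is a feature of 1:1 sampling. In the cohort the lower rate needs more patients below about 35% (167 at 20%, 136 at 30%, 130 at 35%), so planning on a low rate is cautious in that range. No criticism of the choice follows.

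**Section 12.2 tests at 0.05.** At that level the dominant cohort power would be Φ(2.80 − 1.96) = 80%, Φ(3.11 − 1.96) = 87% and Φ(3.13 − 1.96) = 88%. But Section 12.1 attaches its 80% to alpha 0.01, and that is the claim examined here.

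**Conclusion.** The power statement is wrong as written. Within the stated 1:1 design, 112 fits the 20% rate only: power is 77.5% at 30% and 71% at 50%. In the cohort that the protocol describes, 112 patients give about 70% for response at 30%, about 10 points short, and about 71% for neutropenia at 50%, about 9 points short. At the 20% severe-reaction rate that reproduces 112, cohort power is about 59%. Taking the Background's ORR does not restore 80%: dominant cohort power is 72.5% at 35% and 71.1% at 50%.

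These figures rest on a dominant model, 15% as an allele frequency, and effects at the stated bounds. If the intended model was log-additive, the response endpoint at 30% is adequately powered (about 81%), neutropenia at 50% is marginally short (about 79%), and a 20% toxicity rate is short (about 73%). The conclusion for the 20% and 50% rates therefore holds under both models, though its size differs; the conclusion for 30% response needs the dominant model.

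**What to change.** In Section 12.1, GWAS study:

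1. State the genetic model, and whether 15% is an allele or a carrier frequency.
2. Replace the 1:1 ratio with the case fraction expected in the cohort for each endpoint.
3. Restate the power of 112 separately for response and for Grade ≥3 toxicity, at the protocol's own rates. Under the dominant model this is about 70% at 30% response and about 71% at 50% neutropenia.

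The 1:1 figure for response should not be carried into the new text, since it would still overstate power for a cohort. The cost is one reworded paragraph and a less favourable stated power. Enrolment does not change.
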